## **13.2 Sample Size and Power Considerations**

Because this is a proof-of-concept clinical trial, sample size will be determined based on feasibility and study funding. Previous investigations on CBF after 12 weeks of aerobic exercise [47] suggest that 20 participants per group is sufficient to determine response variance and effect sizes to establish preliminary signals of efficacy. Attrition rate is anticipated to be 15%, a conservative estimate, as the attrition rate of previous RT interventions of similar length (12 weeks, 3days/week) in healthy older adults is about 5.7% [131]. Our previous RT intervention in older adult men, upon which the current study’s RT program is based, had no dropouts due to injury, illness, or personal choice [80]. Accounting for 15% attrition (~3) yields a final, proposed sample size of 23.

Sensitivity analysis using these parameters was performed in G*Power 3.1.9.2. With the proposed sample size of 23, we would have sufficient power to statistically detect a large effect size d between dependent means of 0.611 with α = 0.05 and 1-β = 0.80.

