## **1.4 Hypotheses**

1. 12 weeks of periodized RT with short rest intervals improves cerebrovascular function (resting CBF, ATT, and intracranial VC) in healthy older adults 60-80 years of age.
2. A 12-week periodized RT program designed specifically to maximize strength gains improves cognition in healthy older adults.

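### The quoted sensitivity (d = 0.611 at 80% power) counts all 23 enrolled as analysed, although the same section expects about 3 of them to be lost

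*Protocol*

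**What the plan says.** Section 13.2 of the protocol reasons in three steps.

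- A target: earlier work on cerebral blood flow after aerobic training is said to "suggest that 20 participants per group is sufficient to determine response variance and effect sizes". The trial has one group in which each person is their own comparator, so this means 20 people with data.
- An allowance for loss: "Attrition rate is anticipated to be 15%, a conservative estimate", leading to "Accounting for 15% attrition (~3) yields a final, proposed sample size of 23".
- A sensitivity statement, run in G*Power on the inflated number: "With the proposed sample size of 23, we would have sufficient power to statistically detect a large effect size d between dependent means of 0.611". Power is set there at 80% and alpha at 0.05. Whether alpha is one- or two-sided is not stated.

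Four other places bear on the point. Section 13.1 makes the primary endpoint an effect size for the difference between the two periods in the change of the outcome, estimated from an intent-to-treat longitudinal mixed model. Section 3.0 and the calendar in 9.10 place the MRI at baseline, pre-intervention and post-intervention. Section 10.0 ties the endpoint to at least 80% session attendance and to having baseline and post-intervention measurements. Section 5.0 mentions recruiting replacements for people who drop out, with no number or rule.

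**The concern.** The three people are added because they are expected to be lost. The next paragraph then treats them as analysed. An allowance for attrition cannot also supply power.

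The quoted test compares dependent means, so its n is the number of complete pairs. The contrast of interest, change over the training period minus change over the control period, needs all three scans from a person to form a complete observation. Under the section's own attrition assumption, about 20 people provide one.

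The primary objective (Section 2.1) is to establish response variance and effect sizes and to give preliminary signals of efficacy. Anyone planning the next study would read 0.611 as the effect this trial could detect with 80% power, and that is somewhat better than the plan supports.

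**Working it through.** **Inputs, all from Section 13.2:** enrolled n = 23; target 20; attrition 15%, about 3 people; alpha = 0.05; power 0.80; d = 0.611.

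**Method.** Paired t-test with the exact noncentral t distribution: degrees of freedom n − 1, noncentrality d × √n, and power = P(|T| > t at 0.975 on n − 1 df).

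**Step 1: reproduce the plan's figure (n = 23).** Noncentrality 0.611 × √23 = 2.93 on 22 df gives power 79.96%. Solving for 80% power gives d = 0.6113. The stated figure is reproduced, and it is two-sided: one-sided alpha at n = 23 would give d = 0.535, and the two-sided normal approximation 0.584.

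**Step 2: the number the section expects to have.** 23 − 3 = 20.

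**Step 3: repeat with 20 complete pairs.** Noncentrality 0.611 × √20 = 2.73 on 19 df.

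| Complete pairs | d detectable with 80% power | Power at d = 0.611 |
| --- | --- | --- |
| 23 (as stated) | 0.611 | 80.0% |
| 20 (as planned after attrition) | 0.660 | 73.6% |

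The loss is 80.0 − 73.6 = 6.4 percentage points, or 0.660 − 0.611 = 0.049 in detectable d.

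**Step 4: allow for the mixed model.** The contrast is post − 2 × pre + baseline, so c = (1, −2, 1). Let Σ be the 3 × 3 covariance matrix of the three assessments. The information is 20 × Σ⁻¹ plus 3 times the inverse of the block of Σ that the dropouts provide. The effective number of complete participants is (c′Σc) divided by (c′ × information⁻¹ × c). This was evaluated under two assumptions that the protocol does not give: compound symmetry with correlation 0 to 0.9, and data missing at random. Power was taken on 19 to 22 df.

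| When the 3 leave | Effective n | Power at d = 0.611 |
| --- | --- | --- |
| After the pre-intervention visit | 22.2 to 22.4 | 77.9% to 79.0% |
| During the control period | 20.0 to 20.4 | 73.7% to 75.2% |

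The partial data recover some of the loss, most of it if the dropouts are late, but 80% is not reached in either case.

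**The case against.** The case for leaving the section alone has four parts.

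*The calculation is right and says what it is for.* This stands as far as it goes: 0.611 is exact for 23, and the sentence names 23. A reader might infer an arithmetic error, but there is none. What does not fit is the choice of n, given the preceding paragraph.

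*Nothing depends on the figure.* This stands, and it sets the weight of the point. Section 13.2 bases enrolment on feasibility and funding, and Section 13.1 makes the primary endpoint an effect size because the data are preliminary. A reader might infer that the trial is underpowered or must enrol more; the documents do not support that.

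*The mixed model keeps partial data.* This stands in part. The 73.6% is the complete-pairs value and a floor; the range with partial data is about 74% to 79%. The published figure is nevertheless a paired-test figure, and neither reading gives 80%.

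*Dropouts may be replaced.* Section 5.0 does mention this, and full replacement could bring the completers to 23. But it gives no number or rule, and Section 13.2 absorbs the losses inside the 23.

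Some further readings are tempting but do not hold:

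- That the basis should be 19 completers. 23 × 0.85 = 19.55 rounds to 20, and the protocol itself says about 3 are lost. Inflating as 20 × 1.15 = 23 rather than 20 / 0.85 = 23.5, rounded up to 24, differs by one person.
- That 15% is not conservative over the longer calendar. Extending 5.7% per 12 weeks at a constant rate to 31 weeks gives 1 − 0.943^(31/12) = 14.1%, still below 15%.
- That alpha should be split over the three outcomes in Hypothesis 1. The protocol adopts no such correction, and multiplicity is commonly left to the SAP, which is not at hand.

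**Conclusion.** The point holds as a minor inconsistency within Section 13.2. The stated 80% power at d = 0.611 applies only if all 23 participants are complete, and the section plans for about 20. On that basis the detectable effect is d = 0.66 and power at d = 0.611 is about 74% for complete pairs, or about 74% to 79% with partial data in the mixed model.

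The complete-pairs figures rest on a two-sided alpha, inferred because it reproduces 0.611, and on a loss of 3. The upper range also rests on compound symmetry and data missing at random. If dropouts are in fact replaced until 23 people complete, the stated figure would stand, but the protocol would have to say so. The design, the enrolment of 23 and the planned analysis are not called into question.

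**What to change.** Restate the sensitivity in Section 13.2 along these lines: with about 20 participants completing all three assessments, d = 0.66 is detectable with 80% power (two-sided alpha 0.05, a single outcome); power at d = 0.611 is about 74%.

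In the same edit, reconcile this with Section 5.0. State whether dropouts are replaced and, if so, up to what number, or that the 23 already includes the expected losses.

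The cost is a protocol wording change and a slightly less favourable sensitivity figure. No extra enrolment and no change to the analysis is needed.

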# **14.0 Registration Guidelines**

Prospective participants may contact investigators of the study at the CERC located in the Center for Health Professions (CHP149) on the Health Sciences Campus of the University of Southern California, or may call the lab at [contact]. Registration details and additional information will be provided to all prospective participants. All prospective study participants will be required to fill out an informed consent prior to beginning study requirements. Investigators will register patients to the study after the informed consent has been obtained, then participants will be screened to ensure eligibility in accordance with investigation requirements.

Note: At the time of registration, two copies of a signed and dated patient Informed Consent form with Bill of Rights will be available (one copy for the patient; and the other for the PI’s file).

# **15.0 Biohazard Containment**

All blood draws will be performed by a California-State Licensed phlebotomist in a private room designated for blood draws at the CERC. Waste from blood sampling procedures will be handled using universal precautions (e.g., needles/syringes placed in sharps containers, dry waste contaminated with human blood placed in biomedical waste containers).

# **16.0 Ethical and Regulatory Considerations**

All institutional and Federal regulations concerning the Informed Consent form will be fulfilled. The study will be conducted in adherence to ICH Good Clinical Practice.

## **16.1 Risk/Benefit Assessment:**

Potential risks: Participants might experience exercise-related fatigue, dizziness, nausea, strains, and/or soreness. All participants will be supervised through proper warm-up, cool-down, and exercise instruction by an exercise specialist to minimize these discomforts.

There is a chance the subject may experience slight discomfort or nausea during the blood draw. Immediate side effects may include pain or discomfort associated with needle stick as well as possibility of bruising and nerve aggravation at the blood draw site in the antecubital space of the arm. The risks of two blood draws (baseline and post-intervention) are greater than minimal. However, the amount of blood (~20mL per draw) that will be taken per blood draw at only one site on the participant’s body is small.

Potential benefits: There are no immediate benefits to the subject. However, the participants will have the benefit of learning about resistance training program design, their physical fitness, and physical fitness testing, as well as experiencing improvements in overall health due to an exercise intervention. Potential study participants are encouraged to participate if they are interested in research and to further their understanding of resistance training, physical fitness and brain health.

## **16.2 Financial Obligations and Compensation**

There are no financial obligations on the part of the subject. There will be no financial compensation for participation in this study. However, participants will receive supervised RT or flexibility training by a certified exercise specialist.

